## Appendix H: Tools for Collecting Fixed and Variable Costs

| Fixed Costs                   | Variable costs               |
|-------------------------------|------------------------------|
| Training                      | Staff time to deliver SOC    |
| Lay Health Workers            | Staff time to deliver BSMART |
| Research Assistants           |                              |
| Nurse prescribers             |                              |
| Cost of SOC brochure          |                              |
| Cost of data collection tools |                              |
|                               |                              |

|                    |                            |
|--------------------|----------------------------|
| Training Costs     | Cost of training materials |
|                    | Cost of training venue     |
|                    |                            |
| Cost of trainer(s) | Cost of trainers' time     |
|                    | Transportation             |
|                    | Per diem+                  |
|                    |                            |
| Trainee costs      | Transport                  |
|                    | feeding                    |
|                    |                            |

|                  |             |
|------------------|-------------|
| Cost of SOC      |             |
| Staff Time       | Hourly wage |
|                  | Time spent  |
| Cost of brochure |             |

|                           |                                                                                                  |
|---------------------------|--------------------------------------------------------------------------------------------------|
| Cost of BSMART            |                                                                                                  |
| Staff cost for counseling | Hourly wage                                                                                      |
|                           | Time spent                                                                                       |
| Cost of CO monitoring     | coVita CO Smokerlyzer                                                                            |
|                           | Staff time                                                                                       |
|                           | Hourly wage                                                                                      |
| Cost of varenicline use   | Varenicline dose (for 12 weeks)                                                                  |
|                           | Staff time for participant assessment for eligibility for varenicline use                        |
|                           | Patient transportation for drug pick ups                                                         |
|                           | Cost of managing adverse events                                                                  |
|                           | Staff time for adverse event management                                                          |
| Cost of follow-up visits  | Participant transport weekly for the first four weeks and monthly for two months then at week 24 |
|                           | Staff costs for follow-up visits                                                                 |

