### Provision of varenicline

Participants referred for treatment with varenicline will be taught the correct use of varenicline by the nurse prescriber/ dispenser (NPD) at the site where the participant receives care. Participants will initiate medication treatment with varenicline for smoking cessation with a quit date scheduled for day 8 following the first study dose of the medication. Participants will meet with the NPD at baseline who will evaluate them, provide medical clearance and sign off on prescription orders if they meet the requirements for varenicline use (See Appendix IX). Varenicline will be prescribed in accordance with package labeling and provided to participants by the nurse prescriber/ dispenser. Participants will receive a weekly supply of medication for the first four weeks to ensure proper dosing and monitoring for adverse events. For the subsequent eight weeks, participants will return every 4 weeks to receive the next month’s supply of medication. Dosage adjustments will be permitted in an effort to control adverse effects throughout the trial. This will allow us to balance internal validity with good clinical practice.

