### **4. Measures to determine the preliminary cost-effectiveness of BSMART**

Cost components and incremental costs. The cost-effectiveness of interventions will be compared based on the 7-day point prevalence abstinence at 6 months. The analysis will adopt a healthcare system perspective and calculate direct medical costs associated with the implementation of each strategy. Fixed costs include any set-up costs associated with the implementation of the interventions (e.g., supplies, information technology infrastructure, baseline staff training) and will be collected at week 0. Variable costs include ongoing staff or lay case manager and nurse contact time with study participants, and follow-up training (time and material costs). Variable costs will be collected at week 12 and quarterly thereafter. Time will be valued using prevailing wages that are applicable to the staff expertise. The calculation of the 6-month costs for the control and implementation phases will involve summing across each of the cost

components at the individual level to provide an estimate of the period cost (per individual and average period cost for each of the strategies. The incremental cost of the interventions will be defined as the difference in average costs when comparing the implementation period to control period. The incremental cost of implementing BSMART = ((‘component A’ cost per person x number of persons for implementation period) + (‘component B’ cost per person x number of persons for implementation period) +...) – ((‘component A’ cost per person x number of persons for control period) + (‘component B’ cost per person x number of persons for control period+ ...)). The quarterly cost calculation accounts for the censoring of data due to loss to follow-up or administrative censoring using an inverse probability-weighting  approach.

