7. **Adherence to Medication**: Pill and counseling adherence will be assessed at Weeks 0, 1, 2, 4, 8, and 12. Pill adherence will be tracked by the following question at each medication visit: How many days in the last week did you take at least one of your study pills. Pill adherence will be defined by participant self-report of taking six or seven pills at week eight which coincides with their last receipt of varenicline.
8. **Adverse Event Monitoring** (Baseline, weekly for 4 weeks then every 4 weeks until week 12): Adverse events will be monitored at each study contact and classified and graded using the Common Terminology Criteria for Adverse Events and Common Toxicity Criteria provided by the National Cancer Institute. Our protocol for responding to Serious Adverse Events is summarized in the Human Subjects section.  
  
The 5 "A"s (SBIRT) Checklist and the Intake Smoking History Questionnaire will be administered at baseline for PLWH newly enrolling to HIV treatment and those currently on HIV treatment. A Follow-up Smoking Use Algorithm will be administered at baseline and at 4-, 12-, and 24-weeks of follow-up. The CO measurement will be obtained at baseline, 12 and 24 weeks of patient follow-up using coVita CO Smokerlyzer .

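### Appendix H lists the varenicline pick-up trips in two rows of the BSMART cost form, and travel paid by patients falls outside the stated costing perspective

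*Protocol*

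**What the plan says.** The Cost of BSMART table in Appendix H has two travel rows under different components:

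- under varenicline use: "Patient transportation for drug pick ups";
- under follow-up visits: "Participant transport weekly for the first four weeks and monthly for two months then at week 24".

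The Cost of SOC table in the same appendix lists staff time and the brochure, with no travel row.

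The section on cost-effectiveness measures fixes the frame: "The analysis will adopt a healthcare system perspective and calculate direct medical costs associated with the implementation of each strategy". The variable costs it names are staff contact time and follow-up training; participant travel is not among them. It then adds the cost components for each individual and takes the difference between the two phases.

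The dispensing schedule is in the section Provision of varenicline: "Participants will receive a weekly supply of medication for the first four weeks to ensure proper dosing and monitoring for adverse events", and then "For the subsequent eight weeks, participants will return every 4 weeks to receive the next" month's supply. The item on medication adherence refers to a self-report "at week eight which coincides with their last receipt of varenicline".

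**The concern.** The two rows carry different labels, so whoever completes the form could reasonably fill in both. If the second row's weekly and monthly visits are the drug pick-ups, the same journeys enter the participant's cost twice. Nothing in the protocol tells the analyst to use only one row. The control side has no travel row, so nothing cancels in the difference.

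There is also a conflict of scope. A form that collects participant travel sits beside an analysis limited to direct medical costs of the healthcare system. If patients pay for the travel, including it answers a different question from the one stated.

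Objective 4 is meant to inform the Ministry and the national AIDS agency. Both problems push the same way: the intervention would look more expensive per additional abstinent participant than it is under the stated perspective.

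**Working it through.** The protocol gives no fare, trip total or ICER, so there is no figure to reproduce. The check compares visit weeks and then shows how an overlap would carry through.

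**1. Pick-up weeks** (Provision of varenicline; medication adherence item). One-week supplies at baseline and weeks 1, 2 and 3 cover 4 × 1 = 4 weeks. Four-week supplies at weeks 4 and 8 cover 2 × 4 = 8 weeks. The total is 12 weeks, which agrees with week 8 as the last receipt. Pick-ups: {baseline, 1, 2, 3, 4, 8}. The adherence form and the side-effects checklist also carry a week 12 visit. If that is read as a pick-up in place of baseline, the set is {1, 2, 3, 4, 8, 12}.

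**2. Follow-up transport row** (Appendix H). Four weekly trips, two monthly trips and week 24: {1, 2, 3, 4, 8, 12, 24}, which is 7 trips.

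**3. Is that row the research follow-up schedule?** No. Tables 2 and 3 place the follow-up questionnaires at weeks 4, 12 and 24 only. In Table 3, weeks 1, 2, 3 and 8 hold nurse-prescriber entries (adherence and adverse events) and none for the research assistant. The section on adverse-event monitoring ties that monitoring to medication pick-up.

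**4. Overlap.**

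- Week 8 as last pick-up: weeks 1, 2, 3, 4 and 8, so k = 5. If both rows were filled from these schedules, 6 + 7 = 13 trips would be entered for 8 distinct trips.
- Week 12 read as a pick-up: k = 6, with 13 trips entered for 7 distinct trips.

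**5. Effect on the result.** Let t be the cost per trip, u the share taking varenicline, and Δ the difference in abstinence.

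- Excess incremental cost per implementation-phase participant = k × t × u. The incremental net monetary benefit falls by the same amount.
- Excess ICER = k × t × u / Δ, for Δ > 0.

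Δ is 0.10 in the power section and 0.08 in the objectives. Neither t nor u is in the protocol. Purely to show the scale, assume t = $1 to $10 and u = 0.5 to 1.0:

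- k = 5: 5 × 1 × 0.5 = $2.50 to 5 × 10 × 1.0 = $50 per participant; 2.50/0.10 = $25 to 50/0.08 = $625 per additional abstinent participant.
- k = 6: $3 to $60 per participant; 3/0.10 = $30 to 60/0.08 = $750.

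**6. Perspective.** Under the same assumptions, take 13 entered trips for a varenicline user and 3 (weeks 4, 12, 24) for a non-user. All travel left in then adds (13 × 0.5 + 3 × 0.5) × 1 = $8 to 13 × 10 = $130 per participant, or 8/0.10 = $80 to 130/0.08 = $1,625 per additional abstinent participant. This includes the double count in step 5. If patients pay, none of it is a cost to the healthcare system.

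**The case against.** The strongest reply is that Appendix H is a collection form. It has no fields for quantities, unit costs or totals, and it does not say that every row enters the base case. The analysis rule is in the costing section, which does not mention participant travel. Collecting travel data is compatible with omitting it from the base case or using it in a sensitivity analysis, and an analyst could notice the overlap and drop a row. This stands to the extent that the overstatement is conditional. It does not remove the problem, because the protocol's summing rule covers all components and no exception is made.

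A reader might infer a fixed error: 12 post-baseline trips recorded for 7 made (+71%), or 50 surplus trips per additional quitter (5/0.10). The documents do not support this. The pick-up row has no count or schedule of its own. The ratio changes with the treatment of baseline and week 12: 13 to 8 is +63%, and 13 to 7 is +86%. The trips per quitter depend on an assumed full uptake and on whether the effect is 10 or 8 points.

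A reader might also infer that no transport cost belongs in the analysis. That depends on who pays, which the available text does not say; the consent forms, where reimbursement might be described, are not part of it. The costing section also uses direct medical costs loosely, since it includes information technology and training, so that phrase alone cannot exclude transport. If the health system reimburses travel, the perspective objection weakens, but the double entry remains.

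**Conclusion.** The point holds in conditional form. The two travel rows overlap on five post-baseline pick-up trips, or six if week 12 is a pick-up. If both are completed and summed as the costing section describes, incremental cost is overstated by 5 (or 6) × fare × uptake per implementation-phase participant, and the ICER is overstated when the effect is positive. The direction is clear, because the standard-of-care form has no travel row to offset it. The monetary size cannot be established from the protocol; the dollar ranges above rest on assumed fares and uptake.

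Travel paid by patients conflicts with the stated perspective. Whether the travel is in fact paid by patients is not stated in the text available.

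The matter affects Objective 4 only. The primary endpoint and its analysis are untouched. It should be corrected before cost data are analysed.

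**What to change.** 1. Enter each trip once. Either delete the pick-up row, or limit the follow-up row to visits that are not pick-ups. If the pick-up row is deleted, record the remaining row from visits actually made, since participants not on varenicline have questionnaires only at weeks 4, 12 and 24.
2. State in the costing section who pays for participant transport.
3. If patients pay, leave travel out of the base-case ICER and incremental net monetary benefit, and report it only in a sensitivity analysis labelled as patient or societal perspective.
4. If the health system pays, keep the travel once and amend the cost definition in the costing section so that it covers transport.

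The cost is an edit to two form rows and a sentence or two in the costing section. No new data are needed.

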### Follow-up

Research assistants will fill out follow-up smoking questionnaires at weeks 4, 12 and 24 after the patient receives the SOC brochure. Participants will be provided with breath CO measurements using CO Check+

(coVita) at baseline and then weeks 12 and 24 after enrollment. Participants will also be asked to respond to a semi-structured interview at week 24 that explores challenges to smoking cessation, barriers experienced by participants and reasons for success in those who were able to quit successfully.

| Table 2: Participant Timeline- Control Phase |                    |                                           |        |         |         |
|----------------------------------------------|--------------------|-------------------------------------------|--------|---------|---------|
|                                              | Responsible person | 1 st clinic visit/
Baseline | Week 4 | Week 12 | Week 24 |
| Screening of participants                    | LHW case manager   | X                                         |        |         |         |
| Informed Consent                             | Research Assistant | X                                         |        |         |         |
| Enrollment in BSMART study                   | Research Assistant | X                                         |        |         |         |
| Intake Smoking Questionnaire                 | Research Assistant | X                                         |        |         |         |
| Receipt of SOC brochure                      | LHW case manager   | X                                         |        |         |         |
| Follow-up smoking questionnaire              | Research Assistant |                                           | X      | X       | X       |
| Stages of change                             | Research Assistant | X                                         | X      | X       | X       |
| Breath CO                                    | Research Assistant | X                                         |        | X       | X       |
| Semi-structured Interview                    | Research Assistant |                                           |        |         | X       |

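### Appendix H costs CO tests and follow-up visits under BSMART only, although control participants have the same CO tests and research questionnaires; used as written, the form biases incremental cost upward

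*Protocol*

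**What the plan says.** **The cost form (Protocol, Appendix H).** On the standard-of-care side, the variable-cost list has "Staff time to deliver SOC", and the Cost of SOC block breaks this into wage, time and the brochure. The Cost of BSMART block has counselling time and varenicline items, and also "Cost of CO monitoring" (device, staff time, wage), "Staff costs for follow-up visits" and "Participant transport weekly for the first four weeks and monthly for two months then at week 24". A separate varenicline row reads "Patient transportation for drug pick ups". No row for CO, follow-up visits or transport appears under SOC.

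**The visit schedule.** For the control phase, the Follow-up section says: "Research assistants will fill out follow-up smoking questionnaires at weeks 4, 12 and 24 after the patient receives the SOC brochure". CO in that phase is measured with the CO Check+ device ("coVita) at baseline and then weeks 12 and 24 after enrollment"). Tables 2 and 3 show the same CO and questionnaire timings in the two phases, with the research assistant responsible in each. Under Clinical Outcomes, breath CO is what validates the primary endpoint.

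**The costing method (Process and Outcome Measures, section 4).** "The analysis will adopt a healthcare system perspective and calculate direct medical costs associated with the implementation of each strategy". Incremental cost is the sum of components A, B and so on for the implementation period, minus the same components for the control period.

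**The concern.** Objective 4 compares the value of BSMART with standard care, and the Approach section says the result is meant to inform the Ministry and the national AIDS agency. A difference in cost is informative only if items common to both phases appear on both sides or on neither. Here the measurement of the outcome (CO tests and research-assistant questionnaires) is common to both phases, but the form has a place for it on one side only.

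What is at stake is a bias of known direction in the incremental cost, the ICER and the net benefit. It would make BSMART look dearer than it is, for reasons that concern running the trial and not delivering the programme. The primary effectiveness analysis is not affected.

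**Working it through.** The protocol states no unit costs, incremental cost or ICER, so there is no figure to reproduce. The check sets the form beside the schedule and then carries the mismatch through the protocol's own formulas.

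**1. Contacts by phase, and where Appendix H costs them**

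| Item | Control phase | Implementation phase | Row under SOC | Row under BSMART |
|---|---|---|---|---|
| Breath CO (Tables 2, 3) | baseline, weeks 12, 24: 3 tests | baseline, weeks 12, 24: 3 tests | none | yes |
| Research-assistant questionnaire (Tables 2, 3) | weeks 4, 12, 24 | weeks 4, 12, 24 | none | yes, through follow-up staff and transport rows |
| Varenicline supply after baseline (Provision of varenicline) | none | weeks 1, 2, 3, 4, 8 | none, correctly | yes |
| Adherence and side-effect forms at week 12 (Appendices C4, C5) | none | week 12 | none, correctly | yes |

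The incremental number of CO tests is 3 − 3 = 0. The form as written gives 3 − 0 = 3.

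**2. What the follow-up transport row contains**

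Trips: 4 + 2 + 1 = 7, at weeks 1, 2, 3, 4, 8, 12 and 24.
- Weeks 1, 2, 3, 4 and 8 are drug-supply and safety visits, which only BSMART has.
- Week 12 is mixed: the adherence and side-effect forms list it, and it is also a questionnaire and CO visit in both phases.
- Week 4 is likewise a drug-supply visit with a shared questionnaire attached.
- Week 24 is purely an outcome visit and is the same in both phases.

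The wrongly one-sided part is therefore week 24 and the questionnaire element of weeks 4 and 12, not the whole row. The drug pick-up transport row covers weeks 1, 2, 3, 4 and 8 again, so those five trips could be entered twice.

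**3. Bias per person**

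Let c be the cost of one CO test and r₄, r₁₂, r₂₄ the cost of the research-assistant contact at each week. Then

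B = 3c + r₂₄ + r₄ + r₁₂,

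with 3c + r₂₄ as the clear minimum. B is positive for any positive unit cost.

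**4. Effect on the Objective 4 results**

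- ICER = (cost difference) / (abstinence difference), so the ICER rises by B / ΔE when ΔE is positive.
- At ΔE = 0.10 (Power and Sample size): 1 / 0.10 = $10 per extra quitter for each $1 of B.
- At ΔE = 0.08 (Rationale, objective 1): 1 / 0.08 = $12.50 for each $1 of B.
- Net monetary benefit falls by B per person, whatever the willingness to pay.

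**5. Illustration only; these unit costs are assumed and are not in the protocol**

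Take c from $1 to $10 and each research contact from $2 to $20.
- Low end, week 24 only: B = 3×1 + 1×2 = $5. The ICER rises by $50 at 0.10 or $62.50 at 0.08.
- High end, all three contacts: B = 3×10 + 3×20 = $90. The ICER rises by $900 at 0.10 or $1,125 at 0.08.

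The width of this range shows that the size cannot be settled from the document.

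**The case against.** The strongest reply is that Appendix H is a collection form, while the calculation is set in section 4 of Process and Outcome Measures. That formula subtracts the same components for the control period, so shared items would cancel. This is right about the formula, and it is why the bias is conditional on using the form as written. It does not remove the problem: the form asks for no control-phase CO, follow-up or transport cost, so the formula has nothing to subtract. An analyst would have to notice the gap and impute the missing side.

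A second reply is that the transport row is mainly delivery cost. That stands. A reader might infer from seven trips under BSMART and none under SOC that all seven are measurement cost. The documents do not support this, because five trips follow the varenicline supply schedule and week 12 is partly a safety contact.

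A third reply is that research-assistant training and data-collection tools do not show one-sidedness. That also stands. Appendix H puts them in a general fixed-cost list that is not assigned to a phase, and research assistants are trained on standard of care as well. Whether they belong in a programme cost is a question of scope.

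Finally, CO testing might be intended for the scaled-up programme: the protocol describes the device as made for cessation clinics. That is possible, but in this trial research assistants do the tests in both phases on the same schedule, and CO validates the endpoint. A scenario analysis is the right place for it.

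**Conclusion.** The point holds in this form: Appendix H and the section 4 formula do not fit together, and the form used as written overstates incremental cost and understates net benefit. The overstatement equals three CO tests plus the shared research contacts, clearly week 24 and the questionnaire part of weeks 4 and 12. The ICER is overstated whenever the abstinence difference is positive, by $10 per extra quitter for each $1 at 10 points and $12.50 at 8 points.

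The direction rests only on the two schedules and the rows of the form. The size is unknown. A reader might try to express it as a percentage of the drug cost, but without unit costs for CO, visits or transport no such percentage can be supported.

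Participant transport is a separate uncertainty. Under the stated perspective it belongs in the base case only if the health system pays for it, and the document shown does not say who does. Because Objective 4 is a stated, though preliminary, objective and the correction is cheap, the change should be made.

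**What to change.** In Appendix H and in section 4 of Process and Outcome Measures:

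- Exclude outcome-assessment CO tests and research-assistant follow-up contacts from the base-case cost of both phases. Alternatively, add matching rows under SOC and cost these items identically.
- Keep drug-supply, adherence and adverse-event contacts as BSMART costs, including those at weeks 4 and 12.
- Merge the two transport rows so that each drug-supply trip is counted once.
- State whether the health system pays participant transport. If it does not, report transport outside the healthcare-system base case.
- Leave research-assistant training and data-collection tools out of the programme cost, as a matter of scope.

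Excluding the shared items needs only relabelled rows and a sentence in section 4. The matching-rows alternative needs control-phase cost entries that the form does not now request. The downside is one scenario analysis if CO testing is meant to be part of the scaled-up programme.
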